#### Exploratory indicators

2.7.3

We will assess changes in plasma concentrations of CGRP, PACAP, and other biomarkers. Blood samples will be collected at two specific timepoints: baseline and post-treatment. Serum levels of CGRP and PACAP will be quantified using enzyme-linked immunosorbent assays (ELISAs) that have been rigorously validated for clinical trial applications, ensuring reliability, sensitivity, and specificity. Furthermore, correlation analyses will be conducted to evaluate the association between changes in biomarker levels and clinical outcomes, particularly migraine intensity.

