Based on this theoretical framework and incorporating the extensive clinical expertise of TCM specialist [name], we developed the Sishun Formula (SSF) (13). It is a pharmacologically optimized compound comprising five medicinal botanicals (constituent details provided in Table 1), each with documented analgesic and anti-inflammatory properties as evidenced by modern studies (14–18). Our preclinical studies in migraine-model rats demonstrated that SSF significantly reduced serum and trigeminal ganglion (TG) levels of CGRP while elevating 5-hydroxytryptamine (5-HT) concentrations, with concomitant downregulation of nuclear factor-kappa B (NF-κB) and cyclooxygenase-2 (COX-2) protein expression in TG tissues, thereby ameliorating neurogenic inflammation (19).

**Table 1 tab1:** The Chinese herbal components and dose of SSF.

Chinese name	Botanical nomenclature with taxonomic classification	Dosage (g)	Processed botanical material
Guizhi	*Cinnamomum cassia* (L.) J. Presl (Lauraceae)	10	Dried twig
Baishao	*Paeonia lactiflora* Pall. (Paeoniaceae)	10	Dried root
Chuanxiong	Conioselinum anthriscoides “Chuanxiong” (Apiaceae)	10	Dried root and rhizome
Niuxi	*Achyranthes bidentata* Blume (Amaranthaceae)	10	Dried root
Hongjingtian	Rhodiola crenulata (Hook.f. & Thomson) H.Ohba (Crassulaceae)	6	Dried root and rhizome

However, robust clinical validation through randomized controlled trials (RCTs) remains absent, limiting its integration into evidence-based practice. Therefore, this study will implement a multicenter, randomized, double-blind, placebo-controlled trial to further evaluate the efficacy and safety of SSF for acute migraine attacks. By employing the internationally recognized efficacy endpoints and integrating dynamic monitoring of neuropeptide biomarkers, we aim to elucidate the therapeutic mechanisms of SSF within a modern research framework and provide a safe and effective alternative option for migraineurs.

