**Figure 1 fig1:**
[figure not shown]
Study flowchart. SSF, Sishun Formula; VAS, Visual Analogue Scale; MAS, migraine-associated symptom; MBAS, most bothersome associated symptom; CGRP, calcitonin gene-related peptide; PACAP, pituitary adenylate cyclase-activating polypeptide.

**Table 2 tab2:** SPIRIT 2025 participant timeline: schedule of enrollment, interventions, and assessments.

Items	Trial period							
	Screening period	Baseline period	Intervention period (waiting for an eligible migraine attack within 45 days)					Follow-up period
Timepoint	−5 to −1 weeks	−1 to 0 weeks	Within 0.5 h of headache onset	Pre-dose time point after headache onset	0.5 h, 1.0 h post-dose	2.0 h, 4.0 h, 24 h post-dose	48 h post-dose	7 days post-dose
Enrollment								
Eligibility screen	X	X						
Informed consent		X						
Randomization		X						
Intervention								
Sishun Formula, once			X					
Placebo, once			X					
Information collection								
Demographic data	X							
Medication history	X	X						
Migraine episode characterization	X	X						X
Efficacy assessment								
VAS score				X	X	X	X	
Migraine-associated symptoms				X		X	X	
Most bothersome associated symptom				X		X	X	
Migraine recurrence						X	X	
Ying-Wei disharmony syndrome score		X					X	X
Acute analgesic utilization				X	X	X	X	
Plasma CGRP, PACAP, and other indicators		X					X	
Safety assessment								
Complete blood count		X					X	
Urinalysis		X					X	
Liver and kidney function test		X					X	
ECG		X					X	
AE					X	X	X	X
SAE					X	X	X	X

h, hour; VAS, Visual Analogue Scale; CGRP, calcitonin gene-related peptide; PACAP, pituitary adenylate cyclase-activating polypeptide; ECG, electrocardiogram; AE, adverse event; SAE, serious adverse event.

“X” indicates required procedures at designated time points.

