#### Secondary outcomes

2.7.2

The proportion of patients achieving absence of the most bothersome associated symptom (MBAS) at 2 h post-dose. Patients will self-identify their MBAS from the following symptoms at migraine onset: photophobia, phonophobia, nausea, or vomiting.The proportion of patients achieving headache relief at 2 h post-dose. Headache relief is defined as the reduction of initial pain intensity from moderate to severe levels down to mild or no intensity.The proportion of patients sustaining headache relief from 2 to 24/48 h post-dose. Sustained headache relief from 2 to 24/48 h is defined as achieving headache relief without rescue medication use and the absence of moderate-to-severe headache recurrence during 2 to 24/48 h following initial treatment.The proportion of patients sustaining headache freedom from 2 to 24/48 h post-dose. Sustained headache freedom from 2 to 24/48 h is defined as achieving headache freedom without rescue medication use, coupled with the absence of any headache recurrence (mild, moderate, or severe) during 2 to 24/48 h following initial treatment.Change in VAS scores from pre-dose to 0.5, 1, 2, 4, 24, and 48 h post-dose.Time to onset of efficacy, defined as the interval (in minutes) between drug administration and headache relief.Headache recurrence rate between 2 and 48 h post-dose. Headache recurrence is defined as patients who achieved headache relief (freedom) at 2 h post-dose, reexperiencing moderate-to-severe headache (headache of any severity) within the 2 to 48 h post-dose window.Change in TCM “Ying-Wei disharmony syndrome.” The syndrome will be assessed using the Ying-Wei Disharmony Assessment Scale (YWDAS) at baseline, 48 h post-dose, and 7 days post-dose. The scale comprises five core TCM syndromes, and the assessment framework is detailed in Table 3. Its development was grounded in clinical expertise from senior TCM practitioners and integrated classical and contemporary medical literature. Content validity was established through a rigorous review and consensus by a panel of five senior TCM experts. In a pilot study to assess feasibility and inter-rater reliability, all YWDAS assessments were independently performed by two TCM researchers who underwent standardized training using predefined scoring criteria to minimize assessment bias. The inter-rater reliability, assessed by the intraclass correlation coefficient (ICC) for absolute agreement, was 0.76 (95% CI: 0.64–0.84), indicating good agreement.

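### CGRP and PACAP are sampled only at the baseline visit and 48 h post-dose, so the biomarker analysis can describe a late between-arm difference but not the mechanism of acute relief claimed in the Introduction

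*Protocol article*

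**What the plan says.** The Introduction sets the ambition. It speaks of "integrating dynamic monitoring of neuropeptide biomarkers" and continues "we aim to elucidate the therapeutic mechanisms of SSF within a modern research framework". The supporting evidence it cites is from migraine-model rats, in which SSF lowered CGRP.

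Section 2.7.3 (Exploratory indicators) fixes the sampling: "Blood samples will be collected at two specific timepoints: baseline and post-treatment". It then plans the analysis: "correlation analyses will be conducted to evaluate the association between changes in biomarker levels and clinical outcomes, particularly migraine intensity".

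Table 2 gives the timing. The row "Plasma CGRP, PACAP, and other indicators" is marked in two columns only, the baseline period (−1 to 0 weeks, alongside consent and randomization) and 48 h post-dose. The treated attack comes later than baseline, in the column group headed "Intervention period (waiting for an eligible migraine attack within 45 days".

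Pain is recorded on a different schedule. Section 2.7.2 lists "Change in VAS scores from pre-dose to 0.5, 1, 2, 4, 24, and 48 h post-dose", and Table 2 has no VAS at the baseline visit. The primary endpoint (section 2.7.1) is at 2 h.

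Section 2.6 allows conventional analgesics if the trial drug fails in the treated attack. It also allows other acute treatment for non-eligible headaches during the trial.

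**The concern.** The stated aim is to explain how SSF relieves an acute attack, and the trial judges that relief at 2 h. To link a peptide change to the relief, at least one sample has to lie in the interval in which the relief happens. None is scheduled there.

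The biomarker change runs from a visit before the treated attack to two days after a single dose. The change in pain runs from the attack itself. If the two are correlated, the result could reflect the participant's headache state at 48 h, rescue use or the time elapsed between draws as readily as an effect of SSF on the attack.

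What is at stake is interpretation. A null correlation could be read as evidence against the proposed mechanism, and a positive one as evidence for it. The design supports neither reading.

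**Working it through.** The protocol states no figure for this point that could be reproduced. The check is a comparison of schedules, followed by one illustration.

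**1. Schedules side by side (Table 2)**

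| Time | CGRP/PACAP | VAS |
|---|---|---|
| Baseline visit (−1 to 0 weeks) | yes | no |
| Pre-dose, after headache onset | no | yes |
| 0.5 and 1 h | no | yes |
| 2, 4 and 24 h | no | yes |
| 48 h | yes | yes |

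None of the two biomarker samples falls between onset and 2 h. The only time the two rows share is 48 h.

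**2. Interval from the baseline draw to dosing.** Section 2.3.5 counts the 45 days from enrollment, and Table 2 puts consent and randomization inside the baseline week.

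- If the 45 days start at the baseline visit: at most 45 days to dosing, and 45 + 2 = 47 days to the second draw.
- If they start at the end of a full baseline week: at most 7 + 45 = 52 days to dosing, and 52 + 2 = 54 days to the second draw.

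These are upper bounds. Section 2.3.3 requires 2 to 8 moderate-to-severe attacks in 4 weeks, an average spacing of 28/8 = 3.5 to 28/2 = 14 days, so many participants would be dosed sooner.

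**3. Interval from the primary endpoint to the second draw.** 48 − 2 = 46 h.

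**4. What might remain at 48 h (illustration only).** The document gives no peptide kinetics. Assume that a between-arm difference present at 2 h fades exponentially with half-life h. The fraction left is then 0.5^(46/h):

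| Assumed half-life | Fraction left at 48 h |
|---|---|
| 2 h | about 0% |
| 6 h | 0.5% |
| 12 h | 7% |
| 24 h | 26% |
| 48 h | 51% |

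The range runs from nothing to about half. The document does not allow a choice within it.

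**5. The correlation.** Biomarker change is the 48-h value minus the baseline-visit value. VAS change is the value at time t minus the pre-dose value. The starting points differ for every t, and the end points coincide only at t = 48 h. By contrast, the Ying-Wei Disharmony Assessment Scale (YWDAS) is scored at baseline and at 48 h, which matches the biomarker window exactly.

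**The case against.** The biomarkers are labelled exploratory and lie outside the multiplicity families of section 2.11, so no efficacy or safety conclusion depends on them. That stands, and it sets the size of the point.

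A draw inside an unscheduled attack, with dosing within 0.5 h of onset, is hard to arrange, and the 48-h draw coincides with the safety bloods. As a reason for the schedule this is fair. It does not license a mechanistic claim that the schedule cannot support.

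Section 2.7.3 does not say that VAS change from pre-dose is the paired outcome, and the choice of pairing could be left to an analysis plan that is not shown. This stands in part. An analysis plan can choose a matching outcome, as step 5 shows, but it cannot supply a sample that was never scheduled.

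A reader might go further in three ways that the document does not support:

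- That both samples are free of migraine. Participants have frequent attacks, and the baseline draw is not stated to be headache-free. It is certain only that it precedes the treated attack.
- That the 48-h sample has no bearing on the treated attack. It is post-dose, lies within the trial's own 2 to 48 h recurrence window, and may catch a persisting or recurrent headache.
- That a true effect on CGRP would be undetectable. Without kinetics this cannot be said; under the longest half-life assumed above, about half the difference would remain. Nor does the document say whether rescue analgesics change these peptides. It shows only that they may be taken before the second draw.

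**Conclusion.** The point holds as a mismatch between a stated aim and a stated sampling schedule. With draws only at the baseline visit and at 48 h, the trial does not monitor the peptides dynamically through the attack. Its correlation with migraine intensity cannot show how SSF produces relief at 2 h.

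A randomized between-arm comparison at 48 h remains valid as a late effect.

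In size, the baseline draw may precede dosing by up to about 45 to 52 days, and the second draw follows the primary time point by 46 h. The first figure is a worst case that depends on when the 45-day wait starts. The verdict rests on Table 2 alone and needs no assumption about half-life.

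This is a minor point on an exploratory aim. Separately, section 2.7.3 calls the same analytes plasma concentrations in one sentence and serum levels in another, while Table 2 says plasma. The matrix needs to be stated once.

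**What to change.** Keep the draws as scheduled and change the wording and the analysis.

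1. In the Introduction, replace the dynamic-monitoring and mechanism claims with an exploratory aim of describing between-arm differences in CGRP and PACAP at 48 h.
2. In section 2.7.3, make the main biomarker analysis a comparison of the 48-h value between arms, adjusted for the baseline value. Report alongside it rescue use before the draw and the number of days between samples, by arm.
3. Restrict correlations to outcomes on the same window, namely headache state or VAS at 48 h and YWDAS change from baseline to 48 h. Label them non-causal.
4. Name one matrix, plasma or serum, throughout section 2.7.3 and Table 2.

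These are text and analysis changes with no new visits or procedures. The price is a weaker mechanistic claim. Keeping the stronger claim would require a sample taken during the attack, which is an added procedure and not part of this recommendation.

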### Safety assessments

2.8

Safety assessments involve the systematic monitoring of AEs and serious adverse events (SAEs), along with the evaluation of vital signs (including respiratory rate, heart rate, radial pulse, and blood pressure), routine laboratory parameters (such as complete blood count, urinalysis, liver and kidney function tests), and electrocardiograms (ECGs). All assessments are conducted at baseline and 48 h post-dose.

### Sample size and recruitment

2.9

The sample size was calculated based on the primary outcome measure (the proportion of patients achieving headache freedom at 2 h post-dose). Sample size determination derived from the treatment effect of 35% versus 11% placebo response (based on unpublished data), calculated through binomial proportion comparison with one-sided *α* = 0.025, *β* = 0.1, and a 24% superiority margin. This calculation yielded a requirement of 60 participants per arm. To accommodate clinical enrollment uncertainties, including anticipated attrition and protocol deviations, the adjusted enrollment target was set at 144 participants, with 72 in each group. Patient recruitment will be conducted through neurology outpatient clinics and poster-based advertising, leveraging the high patient volume across three centers to ensure sufficient enrollment.

### Data management

2.10

Data management is conducted using the Yidao Research Platform to ensure systematic oversight. Two trained researchers are responsible for entering research data accurately at specified follow-up intervals across all study centers. A comprehensive data cleaning process will be implemented, encompassing automated system checks and manual validation to identify inconsistencies, followed by iterative query resolution between data managers and investigators until all discrepancies are reconciled. Prior to database closure, a formal blind review will be conducted, with the data manager submitting a closure request accompanied by a blind review report and a database closure checklist. This checklist will confirm the completion of six critical criteria: full incorporation of all collected data (including resolved AEs), resolution of outstanding queries, verification of coding consistency, final review of anomalous data, archival compliance with standard operating procedures, and signed approval of the blind review report. Database closure will require documented authorization from stakeholders, after which editing permissions are revoked, with the locking timestamp serving as audit evidence. Post-closure errors will be rigorously documented and assessed for impact on safety/efficacy analyses through multidisciplinary consultation. Database modifications post-lock will require formal approval and restricted access, with relocking procedures mirroring initial protocols. Data integrity is further safeguarded through dual-entry validation, pre-processing audits for missing values and logical errors, and secure archival of source documents by the primary research unit, ensuring full traceability of all corrections via dated, initialed annotations.

### Statistical analysis

2.11

All statistical analyses will be performed using SPSS 25.0 and R 4.3.1 software. Baseline characteristics will be presented through descriptive statistics [mean ± standard deviation or median (interquartile range) or frequency (percentage)]. For between-group balance testing, independent samples *t*-tests will be employed for normally distributed data with homogeneity of variance, while Mann–Whitney *U* tests are used otherwise. Categorical variables will be analyzed using chi-square tests or Fisher’s exact test based on expected frequencies. All predetermined potential confounders will be included as covariates in subsequent models for adjustment, regardless of their between-group balance status. Additionally, baseline variables showing significant imbalance will undergo sensitivity analyses to assess their confounding effects.

Efficacy analyses will be performed on both intention-to-treat (ITT) and per-protocol (PP) populations, with the ITT set including all randomized participants analyzed according to their allocated groups, regardless of protocol deviations, while the PP set will consist of participants who complied with the trial procedures without major deviations. For efficacy assessment, the use of rescue medication before the 2-h time point will be considered a treatment failure for the primary and key secondary endpoints (e.g., headache freedom, headache relief, absence of most bothersome symptom) (26). Accordingly, participants will be included in the 2-h efficacy analysis only if they have not used rescue medication before that time point, even if medication is taken afterward. Similarly, the assessment of sustained outcomes (e.g., sustained headache freedom at 24/48 h) will require no use of rescue medication within the respective 24/48-h timeframe.

The primary efficacy endpoint (2-h headache freedom) will be compared between groups using the chi-square test or Fisher’s exact test, with reporting of risk difference (RD) and relative risk (RR) accompanied by 95% confidence intervals (CIs). For secondary endpoints, categorical variables will be analyzed through logistic regression with baseline covariate adjustment, while continuous variables (e.g., VAS scores) will be assessed using a mixed-effects model for repeated measures (MMRM). Time to onset of efficacy will employ Kaplan–Meier curves with the Log-rank test and Cox proportional hazards models to estimate hazard ratios. To address missing data, multiple imputation will be employed under the assumption of missing at random, using fully conditional specification with predictive mean matching for continuous variables and logistic regression for categorical variables, incorporating baseline and post-baseline covariates; 20 imputed datasets will be generated, and results will be pooled using Rubin’s rules. To control for multiplicity, secondary endpoints will be grouped *a priori* into clinically coherent families, each tested using the Holm–Bonferroni method to control the family-wise error rate. The predefined families are: (1) a 2-h symptom response family comprising absence of the most bothersome symptom and headache relief at 2 h; (2) a sustained efficacy family consisting of sustained headache relief and sustained headache freedom from 2 to 24/48 h; and (3) a time-to-event and recurrence family including time to onset of efficacy and headache recurrence rate. Changes in VAS scores and the TCM syndrome score will be analyzed exploratorily and are not included in the adjustment. Safety analyses will be conducted in the safety set (SS), which includes all randomized participants receiving at least one dose of the study medication. This population will be summarized using descriptive statistics for adverse events, vital signs, and laboratory parameters, with between-group comparisons following the methods used for baseline characteristics.

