### Trial design

2.2

This is a multicenter, randomized, double-blind, placebo-controlled, single-attack clinical trial conducted across three centers: Dongzhimen Hospital affiliated to Beijing University of Chinese Medicine, Xiyuan Hospital of China Academy of Chinese Medical Sciences, and Beijing Tiantan Hospital affiliated to Capital Medical University. A total of 144 eligible participants will be randomized in a 1:1 ratio to either the experimental group (SSF) or the control group (placebo). The study comprises a 4-week screening period, a 45-day intervention period, and a 7-day follow-up period. During the intervention phase, participants will administer SSF or placebo upon experiencing an eligible acute migraine attack, with efficacy and safety assessments conducted at the pre-dose time point after headache onset, 0.5 h, 1.0 h, 2.0 h, 4.0 h, 24 h, and 48 h post-dose. An eligible acute migraine attack must meet two criteria: (1) No prior use of migraine-specific medications (including all Western pharmaceuticals, TCM formulations in any dosage form, or TCM patent medicines explicitly approved for migraine treatment in their prescribing information) within the 24-h period preceding the current episode; (2) The current migraine episode is of moderate to severe intensity [Visual Analogue Scale (VAS) ≥4 scores].

The protocol adheres to the Standard Protocol Items: Recommendations for Interventional Trials (SPIRIT) 2025 guideline (22). The study flowchart is provided in Figure 1, with enrollment, intervention, and assessment timelines detailed in Table 2.

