#### Withdrawal/termination criteria

2.3.5

Participants will be discontinued from the study if any of the following criteria are met:

Patients who voluntarily request to discontinue their participation in the study.Patients who are unable to follow the study procedures or become lost to follow-up during the trial period.Patients who experience serious AEs.Patients with pregnancy detected after trial enrollment.Patients demonstrating absence of an eligible acute migraine attack within 45 days after enrollment.

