#### Primary outcome

2.7.1

The primary endpoint is the proportion of patients achieving headache freedom at 2 h post-dose. Headache freedom is defined as the reduction in headache severity from baseline moderate or severe to no pain, as measured by the VAS.

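### The ITT set and the missing-data rule together impute a 2-hour response for randomised participants who never have an eligible attack and are never dosed

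*Protocol article*

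**What the plan says.** Table 2 of the protocol article places randomisation in the baseline column (−1 to 0 weeks). The next block is headed "Intervention period (waiting for an eligible migraine attack within 45 days", and under Trial design "participants will administer SSF or placebo upon experiencing an eligible acute migraine attack". Section 2.3.5 foresees that some will have no such attack. Among those to be discontinued it lists "Patients demonstrating absence of an eligible acute migraine attack within 45 days after enrollment".

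Section 2.11 describes "the ITT set including all randomized participants analyzed according to their allocated groups, regardless of protocol deviations". It sets no dosing or attack condition. For missing data, "multiple imputation will be employed under the assumption of missing at random", using baseline and post-baseline covariates. The only rule that turns an outcome into a failure concerns rescue medication before 2 hours.

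The primary endpoint in section 2.7.1 is assessed 2 hours post-dose and starts from a headache of a given severity: "Headache freedom is defined as the reduction in headache severity from baseline moderate or severe to no pain, as measured by the VAS". Of the analysis sets in section 2.11, only the safety set has a dosing condition, "which includes all randomized participants receiving at least one dose of the study medication".

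**The concern.** A participant with no eligible attack has no pre-dose VAS score, no dose and no 2-hour time point. The endpoint cannot be evaluated for that person, even in principle. Missing at random presumes that a value exists and was not observed, and here there is none. Read together, the ITT definition and the imputation rule still place this person in the primary denominator and generate a response from baseline data, because no post-dose record exists.

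What is at stake is the meaning of the headline estimate and, in some implementations, its size. The trial asks how a treated attack responds. Depending on how the undefined records are handled, the reported risk difference is either the treated-attack effect with superfluous simulated records or a diluted version of it. The text does not fix which.

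**Working it through.** **Inputs.** Section 2.9: "treatment effect of 35% versus 11% placebo response (based on unpublished data"), one-sided α = 0.025, 90% power, 60 per arm raised to 72. Section 2.3.3: 2 to 8 moderate-to-severe attacks in the past 4 weeks. Section 2.2: a 45-day window. Let f be the never-dosed share, assumed equal in both arms. The article gives no value for f.

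**The plan's own figure.** The unpooled two-proportion formula gives n = (0.35×0.65 + 0.11×0.89)(1.960 + 1.282)² / 0.24² = 59.4, so 60 per arm. This takes the 24 points as the assumed difference. The rise to 72 corresponds to an allowance of 1 − 60/72 = 16.7%.

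**How large might f be?** If eligible attacks follow a Poisson process with r per 4 weeks, P(none in 45 days) = exp(−45r/28).

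| r per 4 weeks | No eligible attack |
|---|---|
| 4 | 0.2% |
| 3 | 0.8% |
| 2 (entry minimum) | 4.0% |
| 1.5 | 9.0% |
| 1 | 20.0% |

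Rates below 2 apply only if eligible attacks become rarer than at entry, for instance because medication in the preceding 24 hours disqualifies an attack.

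**Imputation with arm in the model.** This was simulated with 72 per arm, 20 imputations within arm and 3,000 runs. At f = 16.7% the risk difference was 0.239 imputed and 0.240 in dosed participants only. The standard errors were 0.0733 and 0.0730, and power was 89.9% and 90.2%. With 11% in both arms, rejection was 2.7% and 2.9%. Imputation adds no information and no material bias.

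**Imputation without arm.** Never-dosed participants in both arms then receive roughly the overall response rate, (0.35 + 0.11)/2 = 0.23. The expected difference is [0.35(1−f) + 0.23f] − [0.11(1−f) + 0.23f] = 0.24(1−f).

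**Coding as failures.** The rates become 0.35(1−f) and 0.11(1−f), and the difference is again 0.24(1−f).

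| f | Difference if arm is omitted or failures are coded | Rates under failure coding |
|---|---|---|
| 4% | 23.0 points | 33.6% vs 10.6% |
| 10% | 21.6 points | 31.5% vs 9.9% |
| 16.7% | 20.0 points | 29.2% vs 9.2% |

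**Power.** Exact power of the chi-square test at f = 16.7% is 88.5% with 72 per arm and failure coding. With the never-dosed excluded (60 per arm) it is 90.0%. At f = 10% it is 91.3%, against 91.4% to 91.9% with 64 to 65 per arm.

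**The case against.** The strongest reply is that little is lost in practice. Entry criteria select people with frequent attacks, so f may be only a few per cent. Imputation that includes arm recovers the treated-attack difference. Even at f = 16.7%, failure coding costs about 1.5 points of power. Counting undosed participants as failures dilutes the effect but does not inflate the type I error. All of this stands, and it limits the severity.

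The article also never says expressly that undosed participants are imputed. That follows from applying two general rules together, and a fuller analysis plan could narrow them. As written, though, they have no exception.

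A reader might infer several stronger things that the document does not support:

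- **That 12 of 72 per arm is the plan's own never-dosed rate.** Section 2.9 ties the increase to enrolment uncertainties, including attrition and protocol deviations. It does not mention people without an attack, so 16.7% is only an upper scenario here.
- **That an ITT set of 144 conflicts with a requirement of 60 per arm.** Inflating enrolment while analysing everyone randomised is ordinary practice.
- **That the plan counts these people as failures.** It states no such rule. Failure coding is one possible implementation.
- **That imputation necessarily biases the result.** The simulation shows otherwise when arm is in the model.

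The per-protocol analysis would presumably omit the never-dosed, although its wording does not say so. It also removes other major deviators, so it is no substitute. Whether ITT or per-protocol is decisive is a separate question.

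**Conclusion.** The point holds as a defect in the definition of the primary analysis population, and it should be fixed. Applied as written, the rules impute an outcome that the endpoint definition leaves undefined.

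The harm is mainly conceptual if arm is in the imputation model. Section 2.11 names only baseline and post-baseline covariates for that model, so inclusion of arm is not assured. If arm is left out, or if analysts fall back on failure coding, the risk difference shrinks by the never-dosed fraction: from 24 points to about 23 at 4%, 21.6 at 10% and 20 at 16.7%. These figures assume the planning rates of 35% and 11%, an equal never-dosed share in both arms and, for the likely size of that share, Poisson attacks.

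**What to change.** In section 2.11:

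1. Define the primary efficacy set as all randomised participants who took study medication for an eligible attack, analysed by allocated arm.
2. Limit multiple imputation to dosed participants with missing post-dose ratings.
3. Report the number never dosed by arm.
4. Keep the all-randomised analysis as a sensitivity analysis.

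The restriction should preserve the randomised comparison: whether an eligible attack occurs is settled before dosing and under blinding, so allocation should not influence it. The counts by arm allow this to be checked.

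The cost is a few sentences, with no new data or visits. The primary set will be smaller than 144, and it should be labelled a modified ITT or full analysis set. The change should be made before unblinding.
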